### Qualitative evaluation

At the end of each intervention period a qualitative interview will be conducted by a psychologist. Participating children and young people aged between 8 and 18 years will be offered the choice of joint (children paired with their parents) or separate interviews. Parents will provide consent and children will be asked to assent in qualitative interviews. Interviews will be tape**-**recorded and fully transcribed. Inductive qualitative semi**-**structured interviews will be used to gain a rich, in**-**depth understanding of participants’ experiences and appraisals of oxygen therapy and APAP across age groups and participant status (i.e. patient versus carer).

### Participants

This pilot study will involve 20 participants, recruited regardless of symptoms of sleep**-**disordered breathing, which includes 10 children (age between 8 and 18 years) and 10 adults (age over 18 and above). All participants will be enrolled into the study for 29 days (i.e. 4 weeks).

Consenting participants with HbSS who are aged > 8 years and attend at Guy’s and St Thomas’ NHS Foundation Trust are eligible for this study. Participants will be excluded if they already have overnight respiratory support, if they have existing respiratory or decompensated cardiac failure or if they have any contra**-**indications to APAP therapy. Both inclusion and exclusion criteria are listed in Table 2.

**Table 2 Tab2:** Participant eligibility criteria for participation in the POMS2a trial

Inclusion criteria	
1	Recruitment will be through sickle cell clinics at Guy’s and St Thomas’ (including Evelina Children’s Hospital)
2	Age > 8 years
3	Informed consent with assent in accordance with the institutional policies (UK ethical committee) and European or US Federal guidelines must be signed by the participant or participant's parent or legally authorised guardian acknowledging written consent to join the study. Where appropriate, participants < 16 years will be requested to give their assent to join the study
4	HbSS diagnosed by standard techniques (HPLC, IEF and MS). Participating institutions must submit documentation of the diagnostic haemoglobin analysis
5	Able to speak and understand English
6	Participant or parent/guardian able to use iPad mini via wireless
Exclusion criteria	
1	Participant already on overnight respiratory support, or has used it in the past
2	Hospital admission for acute sickle complication within the past 1 month
3	Participant with > 6 admissions for acute sickle complications within the past 12 months
4	Existing respiratory failure
5	Decompensated cardiac failure
6	History of severe epistaxis
7	Trans-sphenoidal surgery, or trauma that could have left a cranio-nasopharyngeal fistula
8	Perforated ear drum
9	Bullous lung disease
10	Bypassed upper airway
11	Pneumothorax
12	Participant at increased risk of aspiration
13	Pneumocephalus has been reported in a participant using nasal Continuous Positive Airways Pressure. Caution should be used when prescribing APAP for susceptible participants such as those with: cerebral spinal fluid (CSF) leaks, abnormalities of the cribriform plate, prior history of head trauma, and/or pneumocephalus
14	Pregnancy
15	Participants on chronic blood transfusion regimes, or has had blood transfusion within past 3 months
16	Any acute or chronic condition which would limit the participant’s ability to complete the study
Temporary exclusion criteria	
17	Sinus or middle ear infection

### Screening visit

Inclusion and exclusion criteria will be reviewed at the screening visit. After the participant (and parents for paediatric participants) have familiarised themselves with the trial protocol and have given written informed consent, relevant clinical history will be taken.

### Procedure (Table 3, Fig. 1)

**Table 3 Tab3:** Details of study flow and duration of each interventions period

	Screening visit	Trial entry (Day 1)	Days 8–14	Days 15–21	Days 22–28	Day 29
Participant given PIS	x					
Inclusion/Exclusion reviewed	x	x				
Consent signed		x				
Daytime oximetry		x		x		x
Overnight oximeter issued		x				
Oximeter collected			x			
Spirometry		x		x		x
Lung volume testing (adults)		x		x		x
Quality of life evaluation		x		x		x
Blood tests/urine tests		x		x		x
Smartphone issued		x				
Daily pain diary for next week		x	x	x	x	
Intervention 1 commenced			x			
Sleep physiologist to review participant at home to set up intervention 1, review participant and adverse events			x			
Intervention 1 stopped (courier to pick up)				x		
Intervention 2 commenced					x	
Sleep physiologist to review participant at home to set up intervention 2, review participant and adverse events					x	
Intervention 2 stopped (courier to pick up)						x
Qualitative interview with participant and parent/guardian				x		x
Medical/nursing review of compliance and adverse event reporting				x		x

**Fig. 1 Fig1:**
[figure not shown]
Flow chart for the interventions and support from the respiratory physiologist

On day 1, the patient will attend the Day Care Unit at the hospital and data including baseline blood tests, PEDS**-**QL quality of life [50], daytime oximetry, will be collected. Adults will undergo lung function (spirometry and lung volume). The participant will be issued with an iPad mini with a validated smartphone app [38] for rating pain and symptom assessment and will be asked to complete daily data collection using this device for the duration of the whole study, taking approximately 5 minutes per day. They will be given an overnight oximeter to take home and will be asked to use this for 2 nights over the next week. The randomization codes will be provided at the start of the study by an independent statistician from the University of Southampton, who will use simple randomization to generate the order.

On day 8, the participant will have the first intervention (intervention 1), either oxygen or APAP, which will be delivered to their home and set up by the respiratory physiologist, or if they prefer, they can take the treatment home after explanation by the respiratory physiologist. They will be asked to use this for 7 nights and will have planned support calls (Fig. 1). The overnight oximeter will be collected by the respiratory physiologist and the data analysed. On day 15 the participant will return to the hospital Day Care Unit for medical assessment, blood tests, PEDS**-**QL quality of life assessment, daytime oximetry and the first qualitative assessment with lung function studies for the adults. Days 16**–**21 will be a washout phase with no intervention given, but ongoing daily data collection via the smartphone app on the iPad mini. On day 22 the participant will have the other intervention (intervention 2) installed at home and they will be asked to use this for the next 7 nights. On day 29, the participant will go to the Day Care Unit at the hospital for medical assessment, blood tests, PEDS**-**QL quality of life assessment, daytime oximetry and lung function tests (adults) and the second qualitative assessment. Adverse events and serious adverse events will be reported to the sponsor (Tables 4 and 5).

**Table 4 Tab4:** Laboratory findings to be reported to the sponsor within a maximum of 7 days

Variables	Measurement level that may be consider as adverse events
Haemoglobin	Fall of > 20 g/l from baseline is significant
Reticulocytes	10–100 x 10^9^ fall < 10 × 10^9^ is significant
Lactate dehydrogenase	Increase of > 1.5 x from baseline is significant.
Bilirubin	Increase of > 1.5 x from baseline is significant
Creatinine	Increase of > 1.5 from baseline is significant
Erythropoeitin	Fall of > 50 % from baseline is significant
Oximetry	Decrease in baseline oximetry of > 3 % from baseline

**Table 5 Tab5:** The relationship between an adverse event and the intervention

Type of adverse events and relationship to the intervention	Description
Unrelated	• No temporal association to study intervention
	• An alternative aetiology has been established
	• The event does not follow the known pattern of response to study intervention
	• The event does not reappear or worsen with re-challenge
Unlikely to be related	• No temporal association to study intervention
	• Event could readily be produced by clinical state, environmental or other interventions
	• The event does not follow the known pattern of response to study intervention
	• The event does not reappear or worsen with re-challenge
Possibly related	• Reasonable temporal relationship to study intervention
	• The event is not readily produced by clinical state, environmental, or other interventions
	• The event follows a known pattern of response to the study intervention or as yet unknown pattern of response
Definitely related	• There is a reasonable temporal relationship to the study intervention
	• The event is not readily produced by clinical state, environmental, or other interventions
	• The event follows a known pattern of response to the study intervention
	• The event decreases with de-challenge and recurs with re-challenge
Unassessable	• Anything that does not fall into the above categories

The qualitative researcher will undertake interviews at the end of both interventions for all 20 participants and 10 parents/guardians to determine participant preference for one or other intervention. Participants will have a phone call at days 9 and 23 from the sleep physiologist to ensure they are using the equipment appropriately, and further phone support will be available if necessary. The sequence of the proposed investigations and the duration of the trial period is given in Table 3 and the participants’ journey through the interventions is shown in Fig. 1.

### Withdrawal criteria

Participants who wish to withdraw from the study are free to do so. If this occurs they will be asked if they would be willing for us to document withdrawal and the reasons. Participants will be withdrawn if they experience a serious adverse event and in this situation they will be asked if they will continue with qualitative assessment if appropriate. The trial intervention will be stopped if participants are admitted to hospital with an acute sickle complication. In this situation they will be asked if they will continue with the qualitative assessment and if they have only have received one intervention, if they would be happy to have the second intervention.

All adverse events will be documented for these participants as if they had remained in the trial. They will be asked to continue with qualitative assessments. Participants who withdraw may be replaced if appropriate participants are available and consent to the study. Participants will continue to be followed**-**up under the normal clinical care pathway at Guy’s and St Thomas’ NHS Foundation Trust. Participants who develop evidence of suppressed erythropoiesis will discontinue the trial. If they have not had a Parvovirus infection, the blind will be broken.

### Interventions

The two interventions in this study are overnight oxygen therapy and APAP. Both APAP and nocturnal oxygen therapy are non**-**invasive. Support from a respiratory physiologist with experience of APAP and nocturnal oxygen therapy will be available to maximise compliance with the interventions (Fig. 1). Details of each of the interventions are listed below:

### Intervention: APAP

The REMstar® Auto System (Philips Respironics, Chichester, UK) is an APAP device designed for the treatment of obstructive sleep**-**disordered breathing. When set in the APAP mode, the system will monitor breathing whilst sleeping and automatically adjust the pressure to overcome upper airway obstruction. APAP will be administered via a nasal or oral**-**nasal mask. APAP will be set at 4 cmH_2_O with an upper limit of 10 cmH_2_O.

### Intervention: oxygen therapy

Nocturnal oxygen therapy: oxygen concentrator device supplied by Philips Respironics (Chichester, UK). Oxygen therapy is administered via nasal cannula or mask depending on participant preference. Nocturnal oxygen therapy will be administered at 0.5 L/min, in children which was the level most commonly used in the previous trial [37] and 1 L/min in adults.

### Adherence to intervention

For the APAP arm, compliance and adherence to treatment will be formally assessed using specially designed software (Encore Pro™ data management software, Philips/Respironics) and a SmartCard that records both qualitative and quantitative data on a single mail**-**in card. This will be assessed at the end of the 7**-**day intervention period. There is no such capability for the oxygen concentrators and the participant/carer will be asked to record the hours of use. The sleep physiologist will phone participants at 24 hours after starting each intervention and mid treatment. They will provide further telephone support should study participants and their family have any questions/issues with the study treatment or if participants identify a problem (Fig. 1).

### Primary outcome

#### Measuring participant benefit

This is a qualitative study looking at participant experience from the transcribed interviews after each intervention as the primary outcome. The participant’s view on feasibility, acceptability and preference will specifically be explored. Established guidelines for thematic analysis will be followed [51] and augmented with charting procedures from framework analysis [52, 53]. First, one researcher will listen to, read and reread the interviews and transcripts. The interviews will be then coded line**-**by**-**line [53]. A coding manual will be created, and codes that appear most useful to the research question will be applied to the rest of the transcripts [53]. This analysis will be iterative, involving constant comparison and refinement between codes and transcripts to ensure that codes are being used consistently and reflect the data. Codes identifying similar aspects of the data will be clustered together under themes and subthemes. Having identified the main themes, participants will be grouped in a chart according to intervention and participant status, and their talk that relates to each of the themes will be summarised (based on the charting techniques described in framework analysis [52, 53].

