## Methods/Design

The study was given approval by NRES Committee East of England – Cambridge South (14/EE/0163) on 3 June 2014. Local ethical permission was granted by Guy’s and St Thomas’ hospital NHS Foundation Trust. This is a pilot cross**-**over interventional trial. Participants will have 2 interventions, overnight oxygen and APAP, for a week each in randomised order (weeks 2 and 4). There will be a week of baseline data collection (week 1), and a week of washout between the interventions (week 3).

Randomisation will be done by simple randomisation by an independent statistician at the University of Southampton. It will not be possible to blind the participant, study co**-**ordinator, sleep physiologist or psychologist to the order of treatment. However, the principal investigator, statistician and technician performing spirometry, i.e. those responsible for documenting the quantitative endpoints, will be blinded to which intervention is given in which order.

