### Statistical analysis

The preliminary data on participant preference and physiology will be analysed at the end of this pilot phase and will be used to make a final decision about which intervention should be used for trial 2b (the Phase 2 study). This is a pilot phase; all statistical analyses will be treated as preliminary and exploratory and will mainly be descriptive [54]. We will investigate factors that influence recruitment rate, acceptability, adherence and loss to follow**-**up. The variability of outcome measures will be reported and any indication of improvement on any of the treatment will be explored informally: e.g. daily pain rate from the smartphone app, admissions to hospital for complications and laboratory parameters. The decision will be made primarily according to participant preference and, if this is at equipoise, on any apparent physiological benefits, e.g. higher daytime oxygen saturations, improved lung function or rates of adverse events. The cost implications will be assessed and relative long**-**term costs to the NHS will be taken into account if there is still equipoise.

The study will be reported in accordance with the CONSORT (Consolidated Standards of Reporting Trials) 2010 statement (Additional file 1) (or latest version if it is available at the time of reporting) [55]. A baseline table will be included to compare important demographic and clinical characteristics between those who started intervention 1 first and those who started intervention 2 first. In total there 3 time points, baseline, after intervention 1 and after intervention 2; all variables will be reported at all 3 time points. Any deviations from the original statistical plan will be incorporated, with full explanation, into a revised version of the protocol.

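### Device order, the only randomised factor, is missing from the primary-outcome chart and the preference rule, so a last-device effect could be read as a device preference or could mask one

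*Protocol article*

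**What the plan says.** All references are to the protocol article.

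- **Design.** Methods/Design describes a two-period cross-over in which every participant uses both devices, in weeks 2 and 4. Only the order is random: "Randomisation will be done by simple randomisation by an independent statistician at the University of Southampton". Under Participants: "This pilot study will involve 20 participants".
- **Primary outcome.** Under Measuring participant benefit the outcome is participant experience from the interviews: "The participant’s view on feasibility, acceptability and preference will specifically be explored". At the charting step, "participants will be grouped in a chart according to intervention and participant status". Qualitative evaluation explains status as patient or carer, so status does not carry order.
- **Decision rule.** Under Statistical analysis: "The decision will be made primarily according to participant preference and, if this is at equipoise, on any apparent physiological benefits". Cost follows if equipoise persists. Order is not mentioned, and no threshold defines equipoise.
- **Where order appears.** The same section says: "A baseline table will be included to compare important demographic and clinical characteristics between those who started intervention 1 first" and those who started the other one. This is the only analysis step in the article that names order.
- **Timing.** Table 3 and the Procedure text place one interview on Day 15, after the first device, and one on Day 29, after the second. The psychologist and the participants know the order.

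**The concern.** The article fixes the dimensions of the primary-outcome chart and the rule for choosing the Phase 2 device, and both leave out the one factor that was randomised. A comparison based on use of both devices is available only on Day 29. By then the second device has just been stopped and the first was stopped two weeks earlier (Day 15 to Day 29). A tendency to favour the most recent device is plausible in that setting.

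Two things could follow if preference is read without regard to order. With unequal orders, the device that more often came last would gain an apparent preference. With equal orders, neither device gains, but a real preference could be diluted towards an even split and send the decision to the tie-breakers. Preference is the leading criterion for the Phase 2 device, so either misreading would affect the main use of the pilot.

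**Working it through.** The article states no threshold, power or effect size for preference, so there is no figure of its own to reproduce.

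**Inputs from the article:** 20 participants, simple randomisation of order, two periods, and a preference based on both devices available only on Day 29.

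**Assumptions, not in the article:**
- Each of the 20 gives one stated preference, independently of the others.
- q is the chance of naming the last-used device when there is no device preference (0.5 means no order effect; 0.7 and 0.8 are shown).
- 13 of 20 is an illustrative majority, and 8 to 12 of 20 is illustrative of near-evenness.

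**Step 1: how unequal the orders may be.** The chance of a split of k:(20−k) or worse, in either direction, is 2 × P(Bin(20, 0.5) ≥ k).
- Exactly 10:10: 17.6%
- 12:8 or worse: 50.3%
- 13:7 or worse: 26.3%
- 14:6 or worse: 11.5%

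**Step 2: no device preference, given the split obtained.** Let m be the number for whom device A came last. The votes for A are Bin(m, q) + Bin(20−m, 1−q), and the expected share is [mq + (20−m)(1−q)]/20. For example, at 14:6 with q = 0.7 the share is (9.8 + 1.8)/20 = 58%.

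| Order split | q | Expected share for device more often last | Chance of 13 or more of 20 for it |
|---|---|---|---|
| any | 0.5 | 50% | 13.2% |
| 12:8 | 0.7 | 54% | 20.3% |
| 12:8 | 0.8 | 56% | 23.2% |
| 14:6 | 0.7 | 58% | 33.4% |
| 14:6 | 0.8 | 62% | 48.7% |

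**Step 3: averaged over allocations.** Each person's order is a fair coin, so the chance of naming device A is 0.5q + 0.5(1−q) = 0.5 whatever q is. The count is then Bin(20, 0.5), and a majority of 13 or more for either device has probability 2 × 0.1316 = 26.3% for every q. The shift in Step 2 is therefore conditional on the split obtained.

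**Step 4: the order-averaged figure.** With no device preference, the proportions naming A are q where A came last and 1−q where it came first. Their simple average is [q + (1−q)]/2 = 50% at any split.

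**Step 5: dilution at 10:10.** Suppose 80% truly prefer A and a share w of participants simply name the last device. The proportion naming A is w + (1−w)(0.8) where A came last and (1−w)(0.8) where it came first.
- With w = 0.5 these are 0.90 and 0.40, pooled 0.65, so the expected counts are 9 of 10 and 4 of 10, or 13 of 20 in all.
- The chance of 8 to 12 of 20 is 3.2% at w = 0, 14.8% at w = 0.25, 38.8% at w = 0.5 and 76.5% at w = 0.75.
- At w = 0.5 it rises from 22.6% to 59.6% if the true preference is 70%, and from below 0.1% to 19.0% if it is 90%.

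**Step 6: cost in precision.** At 14:6, with proportions near 0.5, the standard error of the simple average is √[0.25 × 0.25 × (1/14 + 1/6)] = 12.2 percentage points. The pooled figure has √(0.25/20) = 11.2.

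**The case against.** Several points on the other side are sound.

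- **No order effect is documented.** The article gives neither evidence for nor a size of a last-device effect, so q and w are assumptions. This stands: the text supports only that such an effect could be misread.
- **Randomising order already protects on average.** This also stands (Step 3). The sponsor will, however, have one allocation, and it will be 12:8 or worse about half the time. The larger figures belong to 14:6, which is uncommon.
- **Each device has its own interview.** The Day 15 account of the first device is taken before the second is tried, and it enters the chart under its own intervention. This is a real safeguard for the experience data. It does not cover the direct comparison, which can come only on Day 29.
- **No vote count is prescribed.** The analysis is thematic and exploratory, and pooling over order is an inference from silence. That is fair, and 13 of 20 is only an illustration.
- **Other plans may touch order.** All variables are to be reported after each intervention, and factors influencing acceptability will be investigated. Order is named in neither, and reporting by time point does not cross preference with order.
- **The article is condensed.** A fuller protocol may add order. But the article does state the chart dimensions and the decision rule, and order is in neither.

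A reader might also infer that at 10:10, everyone naming the last device would be false equipoise. It would not: choice that follows recency alone carries no device preference, so equipoise is the right reading. False equipoise needs a real preference that recency dilutes. At 10:10 the simple average also equals the pooled share, so only the split by order adds information.

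**Conclusion.** The point holds in a limited form. Order is the only randomised factor, yet it is absent from the stated chart and from the preference-first rule. If a last-device effect exists, unequal orders could turn it into an apparent device preference. Under the assumed 70% or 80% chance of naming the last device, a 13-of-20 majority for the device more often last rises from 13% to 20% or 23% at 12:8, and to 33% or 49% at 14:6. At 10:10 the pooled share is not shifted towards either device. An 80% true preference with half of participants naming the last device would raise the chance of a near-even result from 3% to 39%.

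The documents do not show that such an effect will occur, nor that the overall rate of false preferences rises; over all allocations it does not. This is a low-severity, inexpensive improvement to an exploratory pilot analysis.

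**What to change.** 1. Add order (oxygen first or APAP first) as a dimension of the framework chart, beside intervention and participant status.
2. Tabulate the preference stated on Day 29 by order, as a 2×2 table.
3. Before judging equipoise, report the simple average of the two order-specific proportions, with the difference between orders beside it.

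No new data, visits or participants are needed. The price is a slightly larger standard error when orders are unequal (12.2 against 11.2 percentage points at 14:6).

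The split would help to reveal dilution but cannot undo it. It is also imprecise: in the 9-of-10 against 4-of-10 example, the difference between orders is 50 percentage points with a standard error of √(0.9 × 0.1/10 + 0.4 × 0.6/10) = 18 points. It should be presented descriptively, in line with the article's own description of its analyses.
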